### Required research

Despite very promising initial evidence from surrogate parameters and secondary data, there is currently little evidence available that points to the effectiveness and efficacy of imparting concrete CME content using the QC format, [27–29].

Evidence is particularly lacking to suggest whether or not controversial topics associated with barriers, such as the MR-related CME content, can be effectively communicated using QC, [23, 27]. For this reason, we see a need, in this study, to evaluate a CME module in terms of improving the rehabilitation-related knowledge and competencies of GPs on the following levels:Subjective GP satisfaction with the CME module,Stability of MR-related attitudes and CME-related knowledge over time, andSubjective and objective changes in CME-related competencies needed to support MR applications.sensitizing for MR as an instrument for prevention

## Methods

### Aims

The primary aims of this study are to implement and evaluate a CME module for all GPs in Saxony-Anhalt focusing specifically on detecting EWA and facilitating access to MR. Data will also be drawn from defined time periods before and after the module.

### Trial design

This study is an open, non-randomised, pre-post-intervention study. Primary and secondary analyses of the data will be undertaken to evaluate the intervention.

Using secondary data from the DRV Mitteldeutschland, responsible for servicing Saxony-Anhalt, the periods of time 6 months before and 6 months after the intervention will be investigated to see how the approval rates change for MR applications made by insured patients for whom the participating GPs have submitted medical reports.

Primary data collection will take place using questionnaires. The satisfaction of the participating physicians with the module will be assessed immediately after completing the continuing education (t1). The influence of the intervention on GP knowledge about and their attitudes towards rehabilitation will be assessed at two different points in time (t0 = immediately prior to the intervention; t2 = 6 months afterwards). The self-rated CME-related competences will be assessed after completing the continuing education (t1) and 6 months afterwards (t2) (Fig. 1).

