**Methods:**

This study is an open, non-randomised, pre-post-intervention study. The intervention involves a CME module for GPs (*n* = 1365) in the German state of Saxony-Anhalt on the topic of medical rehabilitation in connection with the federal German pension fund (Deutsche Rentenversicherung). The module will be initially held as regularly scheduled meetings in moderated GP quality circles (QC), and then offered as a written self-study unit. At the end it will be evaluated by the GPs. The study’s primary focus is on the organizational practice as measured by the number of approved MR applications supported by medical reports submitted by the participating GPs in the 6 months before and 6 months after the CME module. Other study aims involve measuring self-perceived competencies of GPs, as well as their attitudes towards and knowledge of rehabilitation (both upon completing the CME and 6 months later). In addition, the level of satisfaction with the CME module will be analysed among participating GPs and QC moderators (as CME facilitators).

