## Strengths and limitations

Our intervention is important for every participant (QC, postal) and his daily patient treatmentThis study investigates the effect of a CME module focusing on detection of EWA patient needs and access to MR in a pre-post comparison using a large cohort of GPs in the German federal state of Saxony-Anhalt.The evaluation will be done on different levels: subjective satisfaction of the GPs, stability of GP attitudes, knowledge and self-rated competencies regarding rehabilitation over time as well as the objective changes in CME-based competencies as measured in terms of approved MR applications for the participating GPs.We have a self-selection of participants into the two types of interventions, unfortunately we have not a double-blinded randomized study.The self-selection has a significantly influence on results of these interventions.The evaluated CME module uses both the innovative format of the moderated quality circle and the conventional medium of printed materials for independent study, allowing for subgroup analyses of the effectiveness of the two formats.With the accompanying risk of selection bias, recruitment of the GPs permits them to choose between taking the CME module in the QC setting or as independent study.For some participants, there are different starting dates for the pre-post evaluations due to varying meeting schedules for some QCs or as a result of independent study.

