### Secondary objectives

To assess how satisfied participants are with the CME module (QC versus independent study)To establish whether or not the CME module improves self-rated skills (QC versus independent study)To determine whether or not completion of the module leads to a gain in knowledge about rehabilitation (QC versus independent study)To investigate whether or not the module positively influences attitudes towards rehabilitation (QC versus independent study)To investigate whether or not the participation of the moderators in the optional informational meeting has an influence on the results

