### Outcomes

We focusing on self-rated skills (complete specific rehabilitative documents), knowledge (identification of patients with rehabilitation needs), attitudes (increasing of rehabilitation motivation of participants)The participants learn clinical decision making for patients with rehabilitation need.The approval rate of rehabilitation applications for which participating GPs have submitted medical reports during the 6 months before the intervention and 6 month after serves as the measure to assess the objective organizational practice necessary to prepare succesfully supporting medical reports.Measurement of participant satisfaction with the module will be done using adapted items from the HILVE-II questionnaire, [30] and open-ended questions.Perceived professional skills will be assessed using items from the BEvaKomp, [31].Knowledge of rehabilitative medicine will be assessed using validated, reviewed multiple-choice questions dealing with rehabilitative medicine, [32]Attitudes towards rehabilitation will be captured using items developed by the study authors.

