## Conclusion

Implementing targeted CME on complex topics such as those involving barriers is possible, even promising, when using QCs and their moderators. Of particular importance is how aware moderating physicians are of the relevance of MR need detection and access. We evaluate for the first time a CME module specifically designed to improve the rehabilitation-related expertise and competencies held by GPs in regard to a) subjective physician satisfaction with the CME module, b) stability of CME-based knowledge and attitudes over time, and c) changes in the objective and subjective MR-related competencies needed to support MR applications by comparing QC participants with the study participants who elected to cover the material individually.

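### Self-rated competence has no pre-module measurement, so the secondary objective that the module improves self-rated skills cannot be shown as a measured pre-to-post change

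*Protocol article*

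**What the plan says.** The Trial design section of the protocol article gives each questionnaire outcome its own times. Satisfaction is taken at t1. Knowledge and attitudes are taken at two times ("t0 = immediately prior to the intervention; t2 = 6 months afterwards"). For competence the text reads: "The self-rated CME-related competences will be assessed after completing the continuing education (t1) and 6 months afterwards (t2". The Methods part of the Abstract is consistent with this for competence, since it speaks of "measuring self-perceived competencies of GPs, as well as their attitudes towards and knowledge of rehabilitation (both upon completing the CME and 6 months later".

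The aims for the same outcome are worded in two ways.

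- **Improvement or change.** Secondary objectives: "To establish whether or not the CME module improves self-rated skills (QC versus independent study". The Conclusion lists "changes in the objective and subjective MR-related competencies needed to support MR applications". The Abstract (Background) and the Required research section also list subjective change in competence, as an item separate from the stability of attitudes and knowledge.
- **Stability.** Strengths and limitations names "stability of GP attitudes, knowledge and self-rated competencies regarding rehabilitation over time".

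On the instrument, the Outcomes section says only: "Perceived professional skills will be assessed using items from the BEvaKomp".

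**The concern.** Improvement is a difference between a value after the module and a value before it. Knowledge and attitudes have a t0 value under the Trial design section; self-rated competence does not. Both formats receive the module, so no untreated group can stand in for the missing baseline.

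Two claims are at stake. The first is that self-rated skills rose with the module. The second is that they rose more in one format than in the other. Physicians choose their own format, and Strengths and limitations accepts that this self-selection affects the results. A post-module difference between formats may therefore simply be one that existed beforehand.

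**Working it through.** No sample size, power or significance level is stated for this outcome, so there is no figure to reproduce. The check is to compare the schedule with the objective and ask which contrasts the data can estimate.

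**Step 1: times available** (Trial design)

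| Outcome | t0 | t1 | t2 |
|---|---|---|---|
| Knowledge, attitudes | yes | – | yes |
| Self-rated competence | – | yes | yes |

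**Step 2: contrasts for self-rated competence**

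- Improvement = t2 − t0 (or t1 − t0). Not estimable, because t0 is not measured.
- Retention = t2 − t1. Estimable. It shows whether the post-course rating holds or fades. A gain that is fully kept gives zero.
- Format contrast = quality circle minus independent study, at t1 or t2. Estimable only as a difference in level.

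**Step 3: what the format contrast contains.** For each format, level at t2 = level at t0 + gain. Hence

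difference in level at t2 = difference in level at t0 + difference in gain.

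Only the left side is observed. Without randomisation the first term on the right cannot be taken as zero, so the difference in gain is not identified.

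**Step 4: illustration.** The article gives no scale, so assume one running from 1 to 5, with mean ratings of 3.5 at t1 and 3.3 at t2.

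- Retention: 3.3 − 3.5 = −0.2, whatever t0 was.
- If t0 was 2.5: gain at 6 months = 3.3 − 2.5 = +0.8.
- If t0 was 1, the lowest possible: 3.3 − 1 = +2.3.
- If t0 was 5, the highest possible: 3.3 − 5 = −1.7.

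The same t1 and t2 data fit any 6-month change from −1.7 to +2.3. The extremes are not plausible; they show that the planned data alone set no limit beyond the ends of the scale. The article does not say that t2 − t1 will be reported as the change. It is simply the only within-person difference the schedule allows.

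**The case against.** **The items may ask for gain.** The wording of the BEvaKomp items is not shown. If they ask physicians how much they gained, or how they would have rated themselves beforehand, measuring only at t1 and t2 is coherent. The outcome is subjective by design, so a rated gain is not illegitimate. This stands in part: it would support a claim of perceived improvement, weaker than a measured change. The article does not say that the items work this way.

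**The aim is stability.** Strengths and limitations words it so, and t1 and t2 answer that directly. But the Abstract, Required research and Conclusion keep stability for knowledge and attitudes and place competence under change, and the objective itself says *improves*. The wordings need reconciling.

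**The objective is comparative.** Post-module levels can be described by format, but by Step 3 a level difference is not a difference in improvement.

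**Adjustment is possible.** A reader might infer that the format comparison cannot be adjusted at all. The article does not support that: t0 knowledge, t0 attitudes and approvals in the 6 months before the module are baseline information. They are partial proxies and do not replace a baseline of the same outcome.

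**The article is condensed and an analysis plan may exist.** True, but the article states these times outright, and no analysis plan can supply a measurement that was not taken. Figure 1 is not shown; the text that cites it gives t1 and t2.

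**Conclusion.** The point holds for measured pre-to-post improvement. Under the stated schedule that change is unidentified for every participant, and the format comparison has no baseline of the same outcome. This rests on reading the times in the Trial design section as complete, which the Abstract supports, and on the items rating current competence. If they rate gain, the supportable claim becomes perceived improvement; the questionnaire should be checked.

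A reader might go further and infer that the competence data answer nothing, or that the trial's main result is in doubt. Neither follows. The data can address retention and describe post-module levels. The defect concerns one of five secondary objectives, and the primary outcome, which uses pension fund data from 6 months before and 6 months after the module, is untouched.

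**What to change.** **If t0 has not passed for some or all participants:**

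- Add the same self-rated items to the t0 questionnaire that the Trial design section already schedules for knowledge and attitudes.
- Confirm that a t0 form is collected from self-study participants. The Data management section names t0 forms only for quality circle participants; for self-study it lists consent forms, evaluation questionnaires and exams.
- Define improvement as t2 − t0, with t1 − t0 supportive, and retention as t2 − t1.
- Adjust the format comparison for the t0 score. This deals with prior self-rated competence but not with every effect of self-selection, and the change within each format remains uncontrolled.

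**If t0 has passed:** restate the objective as retention of self-rated skills from t1 to t2, or as perceived gain if the items ask for it, and drop *improves*. Bring the Abstract, Required research, Strengths and limitations, and Conclusion into line. Describe any format contrast as a difference in post-module level between self-selected groups, with the available baseline proxies used and named as such.

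**Cost:** a slightly longer t0 form, plus possibly a new t0 form in the self-study group; or, in the second case, a narrower claim. The primary outcome needs no change.

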**Fig. 1 Fig1:**
[figure not shown]
Trial design of our study: an open, non-randomised, pre-post-intervention study. The intervention (quality circle / postal) involves a CME module for GPs

### Participants & recruitment

General practitioners (i.e. specialists in General Practice, specialists in internal medicine working in Primary Care) participating in special forms of additional compensation schemes (HzV) in Saxony-Anhalt were recruited for this study.

Physicians participating in HzV are required to regularly attend QC as part of an ongoing obligation to pursue continuing education and professional training. This applies to 90% of all GPs in Saxony-Anhalt. At the start of the study, in Saxony-Anhalt 145 GPs served as QC moderators for 1220 GPs (HzV) as potential QC participants.

The initial recruiting phase relies on the QC moderators: all 145 moderators will be informed about the module and invited to an informational meeting on the module. Regardless of whether or not the moderators attend this informational meeting, materials on the module and its evaluation will be sent to all 145 moderators for use in their QCs. Both, the conduction of the module and participation in the study are voluntary for the moderators. Moderators who decide to implement the module will distribute pertinent information about this interventional study and the CME module to their QC participants and then conduct the module in the form of on-site meetings.

During the second recruiting phase, information on the study and continuing education module will be sent to all HzV physicians who have not participated in a rehabilitation-related QC to offer them the option of covering the material as an independent study unit. The physicians who elect this option and opt to participate in the study will return the necessary forms to the study centre. Randomisation will not take place since GPs voluntarily decide to participate in the QC or independent study (Fig. 1).

### Primary objective

This study seeks to establish whether or not the CME module “Medical rehabilitation provided by the German pension fund” improves the organizational practice of GPs as they prepare medical reports in support of applications for MR.

### Secondary objectives

To assess how satisfied participants are with the CME module (QC versus independent study)To establish whether or not the CME module improves self-rated skills (QC versus independent study)To determine whether or not completion of the module leads to a gain in knowledge about rehabilitation (QC versus independent study)To investigate whether or not the module positively influences attitudes towards rehabilitation (QC versus independent study)To investigate whether or not the participation of the moderators in the optional informational meeting has an influence on the results

### Outcomes

We focusing on self-rated skills (complete specific rehabilitative documents), knowledge (identification of patients with rehabilitation needs), attitudes (increasing of rehabilitation motivation of participants)The participants learn clinical decision making for patients with rehabilitation need.The approval rate of rehabilitation applications for which participating GPs have submitted medical reports during the 6 months before the intervention and 6 month after serves as the measure to assess the objective organizational practice necessary to prepare succesfully supporting medical reports.Measurement of participant satisfaction with the module will be done using adapted items from the HILVE-II questionnaire, [30] and open-ended questions.Perceived professional skills will be assessed using items from the BEvaKomp, [31].Knowledge of rehabilitative medicine will be assessed using validated, reviewed multiple-choice questions dealing with rehabilitative medicine, [32]Attitudes towards rehabilitation will be captured using items developed by the study authors.

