### Data management

Attendance records, consent forms and the questionnaires (t0, t1) for the QC participants will be compiled by the moderators and forwarded to the study centre. Those participating in the self-study option will be responsible for sending their consent forms, evaluation questionnaires and completed exams to the study centre.

At the study centre data will be compiled and kept by a custodian who is responsible for sending a list of the study participants to the DRV, where using billing data for each physician, the number of approved MR applications will be determined and reported to the study centre. The questionnaire for the follow-up survey (t2) will be sent out by the custodian. All data shall be compiled by the custodian using identification numbers and forwarded in pseudonymised form to the authors for analysis.

Data sharing is not applicable to this article. The datasets were analyzed during the current study.

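### The primary construct is measured by a count of approved applications in two sections and by an approval rate in two others, and the described DRV transfer names no denominator for the rate

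*Protocol article*

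**What the plan says.** The primary objective asks whether the module "improves the organizational practice of GPs as they prepare medical reports in support of applications for MR". Four places in the Protocol article bear on how this is measured:

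- **Abstract, Methods** gives a count: "The study’s primary focus is on the organizational practice as measured by the number of approved MR applications", compared between the 6 months before and the 6 months after the module.
- **Trial design** gives a rate. DRV secondary data are to show "how the approval rates change for MR applications made by insured patients for whom the participating GPs have submitted medical reports".
- **Outcomes** gives a rate: "The approval rate of rehabilitation applications for which participating GPs have submitted medical reports during the 6 months before the intervention" and the 6 months after it is the measure of objective organizational practice.
- **Data management** gives a count. Once the DRV has received the participant list from the custodian, the next step is this: "using billing data for each physician, the number of approved MR applications will be determined and reported to the study centre".

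No section provides for the number of submitted, decided or rejected applications to be transferred, and none names another source for it.

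**The concern.** A number of approvals and a share approved are different outcomes. The count depends on how many applications a GP supports and on how many of those succeed. The rate depends only on the second.

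The Intervention section says the module works on both: recognising need, which should change volume, and guidance on writing reports, which should change the share approved. A change in one measure therefore need not come with a change in the other, and the two could move in different directions.

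The study's main conclusion rests on this measure. If the data request follows Data management as written, the study centre receives a numerator and the rate has nothing to be divided by. If both definitions stay in the article, a reader of the results cannot tell which one was meant to carry the primary objective.

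**Working it through.** **1. Which measure is primary.** Only the Abstract attaches the word primary to a measure, and that measure is the count. Outcomes does not call the rate primary. The link is indirect: organizational practice is the Primary objective, and Outcomes makes the rate the measure of organizational practice. One construct therefore has two measures.

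**2. What the data flow supports.**

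| Section | Measure | What it needs |
|---|---|---|
| Abstract, Methods | Count | Approvals |
| Trial design | Rate | Approvals and a denominator |
| Outcomes | Rate | Approvals and a denominator |
| Data management | Count | Approvals (the only quantity named) |

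The count can be obtained from the described transfer. The rate cannot.

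**3. Whether the difference matters.** The article has no sample-size or power figure to reproduce on this point. The background section on the role of the general practitioner gives about 1,700,000 applications and 1,300,000 approvals a year:

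- Overall approval rate = 1,300,000 / 1,700,000 = 0.765, or 76.5%.

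Everything below uses assumed volumes and assumed post-module rates and is illustrative only. With approvals = applications × rate and 100 applications before the module, approvals before = 100 × 0.765 = 76.5.

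| Applications after | Rate after | Approvals after | Change in count | Change in rate |
|---|---|---|---|---|
| 100 | 71.5% | 71.5 | −6.5% | −5 points |
| 120 | 76.5% | 91.8 | +20.0% | 0 points |
| 120 | 71.5% | 85.8 | +12.2% | −5 points |
| 150 | 71.5% | 107.2 | +40.2% | −5 points |
| 150 | 81.5% | 122.2 | +59.8% | +5 points |

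Over volume growth of 0 to 50% and rate changes of −5 to +5 points, the change in the count runs from −6.5% to +59.8%. The sign of the change in the count does not determine the sign of the change in the rate.

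**4. Whether the rate can be recovered from the count.** Suppose 92 approvals are reported. A rate of 70% implies 92 / 0.70 = 131 applications, and a rate of 85% implies 92 / 0.85 = 108. Both fit the reported number equally well, so approvals alone say nothing about the rate.

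**The case against.** The strongest reply is that this is a condensed article. The transfer sentence in Data management is not a field list and does not say that approvals are all the DRV will return. Trial design foresees DRV data on approval rates, and a full extract specification may exist elsewhere. This stands as a limit on the point. A reader might infer that the rate can never be computed, or that the DRV will return approvals and nothing else. The article supports neither. It supports only that the one described transfer provides no denominator. The reply does not remove the disagreement between the Abstract and Outcomes, which is stated text and not an omission.

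A second reply is that the count may be the intended measure. The Abstract ties the word primary to it, Data management matches it, and the Aims section speaks of detecting endangered work ability and facilitating access to rehabilitation, which volume can reflect and a rate cannot. This also stands. A reader might infer that the rate is plainly the right choice because the Primary objective concerns report preparation, but the article does not settle that. If rate is only loose wording for a count, Trial design and Outcomes still need correcting.

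Third, the example is constructed. The 76.5% is an overall figure, not the rate for reports by participating GPs in Saxony-Anhalt, and the volumes and later rates are invented. It shows that the measures could diverge. It does not show that they will, or by how much. Likewise, a reader might infer that the favourable measure will be chosen after the data are seen. That depends on whether an analysis plan or full protocol not shown here fixes the measure, so it is not claimed.

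**Conclusion.** The article contradicts itself on the measure of its primary construct: a count in the Abstract and Data management, a rate in Trial design and Outcomes. As the data flow is written, the rate has no denominator. This rests on the text alone and needs no numerical assumption.

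The practical size of the contradiction is not known from the article. Under the assumptions shown, approvals could rise by 12.2% while the rate falls by 5 points, so the choice of measure could decide the direction of the primary result. The documents do not establish which measure is correct. The correction is needed because the main conclusion depends on it and because a denominator that is not requested may not be available later.

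**What to change.** Name one primary measure and use it in the Abstract, Trial design, Outcomes and Data management.

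- **If the rate is kept**, which matches the report-preparation wording of the Primary objective, define the denominator once. One option is decided applications that carry a report from the participating GP. Have the DRV return that same denominator together with the approvals, per GP and per 6-month window, and report the count of approvals beside the rate.
- **If the count is kept**, correct Trial design and Outcomes, and state that the count reflects application volume as well as report quality.

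The cost is a change of wording and, for the rate, an additional quantity in the DRV request. No extra participants or questionnaires are needed. Whether the DRV's per-physician data hold the denominator is not stated in the article and must be confirmed with the DRV before the rate is adopted.
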